## Introduction

### Background and rationale

Medication overuse headache generally refers to monthly headache days of ≥15 per month resulting from acute “medication overuse” (MO) defined as the frequent consumption of acute pain medications above a certain threshold (e.g., 10 or 15 days per month depending on the medication type) for ≥3 months. Diagnostic criteria for MOH were introduced in the International Classification of Headache Disorders, 2nd edition (ICHD-2) (1) without a the requirement of the diagnosis of chronic migraine (CM; see Appendix for details on MOH and CM). In the third edition beta version (ICHD-3β), updated in 2013, concurrent CM and MOH are diagnosed if both criteria are met (2). These criteria remain the same in the ICHD-3 criteria.

The prevalence of MOH is still uncertain (3) and varies from 2% in a recent population-based study (4) to 60% in the Global Burden of Disease Study (5). Whether MOH is a cause or consequence of frequent acute medication intake has been debated for years (6, 7). Nonetheless, MO and MOH management are important in clinical care. MO is associated with an increased risk of chronic headache (8) and chronic migraine (9, 10).

Prognosis of MOH due to different type of chronic headache is probably variable. Although there is evidence that chronic tension-type headache (CTTH) and CM may have partly distinct pathophysiological mechanisms, clinical experience suggests that these two clinical entities may be at opposite poles of a single disease spectrum (11, 12). Of note, CM with MO represents a more severe subgroup of patients and can be difficult to treat (13). In a preplanned subgroup analysis that evaluated efficacy and safety of erenumab in patients with CM and MO, the medication overuse subgroup had a higher proportion of failing to respond to preventive treatment (14).

Effective education for people with MOH plays a major role in effective withdrawal therapy. Successful educational interventions rely largely on a productive doctor-patient alliance (15) and patients' motivation for adherence. In addition, it is often recommended to add a preventive therapy or optimize existing preventive regimens to reduce the number of monthly headache days, improve sense of self efficacy and as a result reduce both the physical and psychological need for acute medication for migraine. Preventive treatments may be pharmacologic, non-pharmacologic, or both.

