## Methods: Participants, interventions, and outcomes

### Study setting

Eligible patients will be screened at neurological outpatient clinic from three study sites at different provinces in China: Affiliated hospital of Yunnan University, Kunming, Yunnan; Xiangya Changde Hospital, Changde, Hunan; and Affiliated hospital of Chengdu University, Chengdu, Sichuan; and Puer People's Hospital, Puer, Yunnan. These sites are all tertiary hospitals which may provide extensive healthcare service for persons with headaches.

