### Sample size

We will estimate each of the above mentioned variables to calculate endpoints for MOH studies according to a published study (22). Hypothesis test will be 2-tailed with 90% power and a significance level of *P* < 0.05. Sample size estimations for the four recommended endpoints are provided in Table 2.

**Table 2 T2:** Sample sizes estimation for each critical endpoint.

**Endpoints**	**Target power**	**Alpha**	**N1**	**N2**	**N**	**Assumed proportion (or mean) for treatment group**	**Referred proportion (or mean ±SD) for control group^*^**	**Difference between groups**
Reduction in monthly headache days	90%	0.05	77	77	154	46%	22%	24%
Cured medication overuse headache	90%	0.05	44	44	88	90%	62%	28%
Headache intensity	90%	0.05	22	22	44	20.7	38.4 ± 17.4	17.7

* Data referred for sample size estimation are all obtained from a published study (reference 16) which enrolled patients with medication overused headache who were assigned to restricted acute medication intake group (allowing to take up to 2 days a week with analgesics or migraine medication during the study period).

Finally, we assume group sample sizes of 77 in gastrodin group and 77 in the control group will achieve 90.188% power to detect a difference between the group proportions of 24%. The proportion in the gastrodin group is assumed to be 22% under the null hypothesis and 46% under the alternative hypothesis. The proportion in control group is 22% based on previously published literature (22). The test statistic used is the two-sided *Z*-Test with unpooled variance. To allow for 20% dropouts, we will include 186 patients, corresponding to 93 in each group.

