## Methods: Assignment of interventions

### Allocation

#### Sequence generation

The external block randomization process will take place at Yunnan University. The project statistician will create a randomized treatment allocation schedule using SPSS by generating 186 numbers. Patients who fulfill criteria for enrollment will be randomly assigned to receive gastrodin or placebo according to a centralized randomization schedule in blocks of 4, stratified by gender and headache frequency at baseline (<14 vs. >14 days per month), to achieve between-group balance in the baseline. Subjects will be assigned to the next available medication number within the block.

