### Statistical methods

All analyses on efficacy endpoints will be performed using the intention-to-treat (43) principle which includes all randomized patients who had an evaluable baseline period of eDiary data (week-0), received at least 1 dose of gastrodin or placebo, and had at least one evaluable follow-up appointment. Safety evaluations will be performed consisting of all participants who received at least 1 dose of study intervention.

Continuous variables are presented as mean ± standard deviation (44) conforming to the normal distribution and median (interquartile range; IQR) for the skew distribution data. Student's *t*-test and Mann-Whitney *U*-test will be used to test differences in continuous variables where appropriate. Categorical variables will be expressed by the number and percentage of occurrences. Differences between two groups will be compared using chi-squared tests or Fisher's exact test where appropriate.

Cox proportional hazard regression (backward stepwise method) analysis and the Kaplan-Meier survival curve will be performed when necessary.

To more completely understand the clinical meaningfulness of the new therapy for MOH results from different headache type, we will conduct a subgroup analysis based on prior headache type (CM/CTTH or CM/ other types of headaches) for all the efficacy endpoints.

Participants who do not complete or are lost to follow-up will be coded as treatment failure, missing values will be handled using multiple imputation method under the missing-at-random (MAR) assumption (45).

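### The arms are compared with unadjusted tests that leave out baseline factors the trial already collects, among them pre-existing headache type, and also centre: a loss of efficiency, not a bias

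*Protocol article*

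**What the plan says.** Under Sequence generation, allocation is in blocks of 4 from one centralised schedule, "stratified by gender and headache frequency at baseline". The frequency levels are below 14 and above 14 days per month. Neither headache type nor centre is a factor.

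Under Statistical methods, continuous endpoints are compared by Student's t-test or Mann-Whitney, and categorical ones by chi-squared or Fisher's exact test. The only model mentioned is a Cox regression with backward selection, to be used if needed and tied to no endpoint. The same section adds: "we will conduct a subgroup analysis based on prior headache type", for all efficacy endpoints.

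On headache type, the Background says: "Prognosis of MOH due to different type of chronic headache is probably variable". Data collection methods lists pre-existing headache type among the baseline variables.

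Study setting speaks of "three study sites at different provinces in China" but names four hospitals, in Kunming, Changde, Chengdu and Puer.

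**The concern.** The protocol expects headache type to matter for outcome, records it at baseline and plans its only subgroup analysis on it. It then leaves it out of both the allocation and the main comparison. The same comparison omits the baseline value of the endpoint, centre, and even gender, on which allocation is stratified.

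Two things are at stake. Outcome variance that these variables could explain stays in the error term, so the trial has less power than its data allow. And if the arms differ by chance in headache type, the primary estimate shifts with no planned correction, and arm sizes within the subgroups become uneven.

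**Working it through.** **1. The plan's own figure.** Inputs from Sample size: "Hypothesis test will be 2-tailed with 90% power and a significance level of" 0.05; "The proportion in the gastrodin group is assumed to be 22% under the null hypothesis and 46% under the alternative hypothesis"; a rate of 22% among controls, taken from a published study; 77 per arm; Z-test with unpooled variance.

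- SE = sqrt((0.46 × 0.54 + 0.22 × 0.78)/77) = sqrt(0.420/77) = 0.0739
- Power = Φ(0.24/0.0739 − 1.96) = Φ(1.29) = 90.1%

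The protocol states 90.188%, so the figure reproduces to within rounding. No covariate enters it. Below, 90% is taken as the starting power.

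**2. What adjustment is worth.** In a linear model whose covariates explain a share R² of outcome variance, the residual variance is (1 − R²) times the total. Then N = 154 × (1 − R²) for equal power, and power at N = 154 is Φ(3.242/sqrt(1 − R²) − 1.96), where 3.242 = 1.960 + 1.282. R² is assumed.

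| R² | N for equal power | Power at 154 | Power after coefficient cost |
|---|---|---|---|
| 5% | 146.3 | 91.4% | 90.3% |
| 10% | 138.6 | 92.7% | 91.7% |
| 20% | 123.2 | 95.2% | 94.4% |
| 30% | 107.8 | 97.2% | 96.7% |

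The last column allows for estimating six covariate coefficients (baseline value 1, gender 1, type in two categories 1, centre 3). Under chance imbalance this inflates the variance by about 1 + 6/(154 − 6 − 3) = 1.041. At R² = 5% the factor is 0.95 × 1.041 = 0.989, so almost nothing is gained. At 20% it is 0.80 × 1.041 = 0.833. A simulation with these six terms agreed: power moved from 89.3% to 89.6% at R² = 5%, from 89.5% to 91.2% at 10%, and from 89.0% to 94.1% at 20% (8,000 runs each).

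**3. Balance in headache type.** With 93 per arm and share p (assumed), the SD of the between-arm difference is sqrt(2p(1 − p)/93).

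- p = 0.3 or 0.7: SD 6.7 points; chance of a gap above 10 points 14%
- p = 0.5: SD 7.3 points; chance 17%

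In simulated blocks of 4 with 186 patients (assuming 70% of one type and 75% women), adding type to gender as a stratifier cut the SD from 6.8 to 1.1 points and the chance of a gap above 10 points from 13.5% to about zero.

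**4. Stratification or adjustment?** Simulated with 154 patients, 60% of one type, and type the only covariate (6,000 runs per setting):

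| R² | Stratified by type | Power, t-test | Power, adjusted | Type I error, t-test | Type I error, adjusted |
|---|---|---|---|---|---|
| 5.7% | no | 90.0% | 91.1% | 5.8% | 5.6% |
| 5.7% | yes | 90.0% | 91.0% | 4.3% | 5.0% |
| 19.4% | no | 89.9% | 94.6% | 5.0% | 5.0% |
| 19.4% | yes | 91.1% | 94.5% | 2.6% | 4.8% |

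The gain comes from adjusting. Stratifying while keeping the t-test adds little power and makes the test conservative.

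**5. Strata.** Eligibility requires at least 15 headache days per month, so the level below 14 should be empty, and allocation is in effect stratified by gender alone. Replacing frequency with a two-level headache type keeps the planned 2 × 2 = 4 strata.

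**The case against.** **No error is shown.** Randomisation followed by an unadjusted test is valid, and chance imbalance is already allowed for in the type I error and the confidence interval. This stands: a reader might infer bias, and the documents do not support that.

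**The prognostic claim is weaker than it looks.** The Background also says "CM with MO represents a more severe subgroup of patients and can be difficult to treat". A reader might infer that chronic migraine does worse than other headache types within this trial. The next sentence, however, cites a trial in chronic migraine in which the patients with overuse responded less well. The natural contrast is therefore chronic migraine with versus without overuse, and every patient here overuses medication. The same paragraph allows that chronic migraine and chronic tension-type headache may lie on one spectrum. Only the hedged statement about variable prognosis remains.

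**Stratifying gains little.** When the analysis is adjusted, leaving a factor with q degrees of freedom unstratified costs about q/N of precision: 1/186 = 0.5% for type and 3/186 = 1.6% for four centres. Without a centre factor, the largest within-centre arm difference averages about 8 patients (four equal centres), which sounds serious. But 27 versus 19 in a centre of 46 retains 4 × 27 × 19/46² = 97% of that centre's precision. This stands too.

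**Centre effects are not documented.** Education is individualised, but it follows one published strategy and precedes randomisation. Nothing in the protocol shows that outcomes differ by centre. Centre is a conventional, cheap model term and not a demonstrated need.

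**Covariates may be left to an analysis plan.** Often so. Here, though, the article does not stay silent: it names the tests, and they are unadjusted. An analysis plan could still replace them.

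**Conclusion.** The point holds as a modest improvement to the analysis. The stated tests leave out baseline variables the trial already has, including the one it expects to bear on prognosis and uses for subgroups. The cost is some efficiency and some protection against chance imbalance.

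The size rests on assumptions. For R² of 5-10%, power rises from 90% to about 91-93% by the simple formula, and to about 90-92% after the cost of six coefficients. The gain is worthwhile if the covariates, with the baseline value among them, explain 10% or more. The protocol gives neither R² nor the share of headache types. The starting 90% comes from a comparison of proportions, whereas the primary endpoint is a mean reduction, so it is a nominal reference. The formula applies to linear models; for binary endpoints it is only indicative.

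Two stronger readings go too far: that re-stratifying alone would recover precision, and that within-centre imbalance threatens the result. The calculations support neither. Changing the stratifier is free only because the frequency factor, as written, separates no eligible patients.

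**What to change.** **Statistical methods.** Make the primary comparison a linear model for change in monthly headache days with treatment, baseline monthly headache days, gender, pre-existing headache type and centre. For the other endpoints use the same terms with that endpoint's own baseline value where one exists: linear for continuous endpoints, logistic for binary ones. Keep the unadjusted tests as sensitivity analyses.

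**Sequence generation.** Replace the frequency factor with headache type. First define its categories: the pairing in Statistical methods (CM/CTTH, or CM/other types) does not say how a patient is classed. The swap secures balance in the subgroup factor and should not be presented as a gain in precision.

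**Study setting.** Reconcile the number of sites with the four hospitals named, so that the centre term has a defined number of levels.

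**Cost.** No extra patients and no new data. There is slightly more analysis work, since each endpoint needs a model, and headache type must be entered before allocation.

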#### Allocation concealment mechanism

A designated pharmacist, the only person who has access to the randomization list, will provide the investigators at each center with an opaque vial containing the study medication labeled with the patient's sequential identification number from the randomized allocation schedule. Patients, investigators, the sponsor, and trial staff are unaware of the trial-group assignments.

#### Implementation

An independent research nurse in each center prepares the appropriate treatments. The study investigators enroll participants, administer treatment and assess the safety and outcomes.

### Blinding

The patients, nurses, study investigators and statistician are blinded to the result of the randomization process until data analyses are finished. The blind code could be broken by the principal investigator only for safety concerns. Gastrodin tablets and matching placebo will be provided in identical blister cards to maintain blinding of the study.

## Methods: Data collection, management, and analysis

### Data collection methods

Baseline survey and efficacy assessments will be based on information recorded by participants using an eDiary mobile application. Baseline information includes age, educational level (years), any medical history, family history of headache, body mass index, age of headache onset, pre-exiting headache type, monthly headache days, and month medication intake days.

Following variables will be recorded both at baseline survey and each headache attack after randomization: headache characteristics, headache associated symptoms, the headache pain intensity, pain duration of an attack (hours), and acute medication use (type and dosage).

Monthly headache days, month medication intake days, the headache pain intensity, score of HIT-6 and SF-36, treatment failure, drop-outs and any adverse events will be assessed at 4, 8, 12, and 24-week follow-up.

A summary table of eDiary is shown in Table 3. Training for the eDiary will be provided for qualified participants during before randomization.

**Table 3 T3:** Summary of data collection from eDiary.

**Variables recorded**	**Day-28–0**	**At each headache onset after randomization**			
Age	x				
Body mass index	x				
Education years	x				
Age of first headache onset	x				
Any medical history	x				
Family history of headache	x				
Diagnosis of pre-existing headache	x				
Monthly headache days	x				
Month medication intake days	x				
Headache pain characteristics	x	x	x	x	x
Headache associated symptoms	x	x	x	x	x
Headache intensity	x	x	x	x	x
Duration of headache pain (hours)	x	x	x	x	x
Type of acute pain medication intake	x	x	x	x	x
Dosage of acute pain medication intake	x	x	x	x	x

### Data management

All the data will be downloaded from a cloud server after each visit and recorded in the CRF and then entered into SPSS software (version 20.0) by an independent data administrator. Data on identification information from participants will be de-identified in SPSS database.

### Statistical methods

All analyses on efficacy endpoints will be performed using the intention-to-treat (43) principle which includes all randomized patients who had an evaluable baseline period of eDiary data (week-0), received at least 1 dose of gastrodin or placebo, and had at least one evaluable follow-up appointment. Safety evaluations will be performed consisting of all participants who received at least 1 dose of study intervention.

Continuous variables are presented as mean ± standard deviation (44) conforming to the normal distribution and median (interquartile range; IQR) for the skew distribution data. Student's *t*-test and Mann-Whitney *U*-test will be used to test differences in continuous variables where appropriate. Categorical variables will be expressed by the number and percentage of occurrences. Differences between two groups will be compared using chi-squared tests or Fisher's exact test where appropriate.

Cox proportional hazard regression (backward stepwise method) analysis and the Kaplan-Meier survival curve will be performed when necessary.

To more completely understand the clinical meaningfulness of the new therapy for MOH results from different headache type, we will conduct a subgroup analysis based on prior headache type (CM/CTTH or CM/ other types of headaches) for all the efficacy endpoints.

Participants who do not complete or are lost to follow-up will be coded as treatment failure, missing values will be handled using multiple imputation method under the missing-at-random (MAR) assumption (45).

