### Outcome measures

As there is a lack of guidelines for reporting results from clinical trials on MOH, we will adopt Hagen et al.'s suggestion on endpoints for MOH studies in follow-up including headache days/month, acute medication use days/month, headache intensity, cured MOH, and responder rate (37).

Primary efficacy endpoint is reduction in the mean number of monthly headache days from baseline at 24-week follow-up.

Secondary efficacy endpoints include:

a. Headache intensity at 12 and 24-week follow-up. The headache intensity at each headache onset will be measured on a 4-point scale (0 = pain, 1 = mild pain, 2 = moderate pain, 3 = severe pain), and be calculated as the average of headache intensity at each headache onset for 1 month;b. Proportion of cured MOH, defined as a patient does not fulfill the diagnostic criteria for MOH in ICHD-3 at 12 and 24-week follow-up;c. Mean change from baseline in total HIT-6 score and the proportion of patients with a ≥ 5-point reduction in total HIT-6 score (38) at 12 and 24-week follow-up. For total HIT-6 scores, a between-treatment group minimally important difference (MID) has been established as ≥2.3 (39). Additionally, a clinically meaningful change for an individual patient has been defined as a ≥ 5-point decrease in total HIT-6 score;d. 50% responder rate, defined as 50% reduction of from baseline in number of moderate or severe headache days at 12- and 24-week follow-up;e. Treatment failure, defined as use of acute medication intake >2 days per week during 12-week treatment;f. Reduction in the mean number of monthly medication intake days for treatment failures at 12- and 24-week follow-up;g. Quality of life (QoL), as measure by the Short Form 36-Item Health Survey (SF-36) (40) at 12- and 24-week follow-up.

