### Participant timeline

Eligible participants will be enrolled from January, 2023 to December, 2024. During the 28-day screening period, baseline information on demographics, number of monthly headache days, number of monthly acute medication intake days, headache intensity, and sum scores of HIT-6 and SF-36 for the past 4 weeks before randomization will be collected through a patient's headache diary or face to face interview in outpatient clinic. Education on medication overuse using BI strategy (36) will be finished before randomization (Visit 0). Training on the eDiary will be started after a signed consent form obtained from a study participant and prior to the first administration of study intervention. At each visit during the double-blind phase and follow-up (Visit 1–4), outcomes and adverse events will be evaluated correspondingly. Schedule of enrollment, interventions, and assessments following SPIRIT 2013 statement (42) is provided in Table 1.

**Table 1 T1:** SPIRIT flow diagram of enrollment, interventions, and assessments.

**Time point**	**Study period**					
	**Baseline screening**	**Allocation**	**Double-blind treatment period**			**Follow-up**
	**Day-28–0**	**Day 0**	**Week 4 (**±**3 day)**	**Week 8 (**±**3 day)**	**Week 12 (**±**3 day)**	**Week 24 (**±**3 day)**

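### The efficacy set called intention-to-treat omits randomised patients lost before their first evaluable visit, whom the same section counts as treatment failures

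*Protocol article*

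**What the plan says.** All on this point stands in the protocol article, Statistical methods, unless another section is named.

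- Principle: "All analyses on efficacy endpoints will be performed using the intention-to-treat" principle.
- Set: it "includes all randomized patients who had an evaluable baseline period of eDiary data (week-0"), and who also "received at least 1 dose of gastrodin or placebo, and had at least one evaluable follow-up appointment".
- Losses: "Participants who do not complete or are lost to follow-up will be coded as treatment failure".
- In the same sentence, after a comma: "missing values will be handled using multiple imputation method under the missing-at-random (MAR) assumption". No endpoint is attached to either rule.

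Under Outcome measures, treatment failure is itself a secondary endpoint: "Treatment failure, defined as use of acute medication intake >2 days per week during 12-week treatment". The primary endpoint is continuous: "Primary efficacy endpoint is reduction in the mean number of monthly headache days from baseline at 24-week follow-up". The other binary endpoints are cured MOH, 50% response and a HIT-6 reduction of at least 5 points.

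Table 1 and Data collection methods place the post-baseline assessments at weeks 4, 8, 12 and 24. The earliest appointment that can admit a patient to the efficacy set is therefore week 4.

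**The concern.** Receiving a dose and attending an evaluable visit both happen after randomisation. A set that depends on them is a modified intention-to-treat set, and a result from it would be reported under a name that promises more. The visit condition is the one that matters, because it removes every patient lost before the first evaluable visit.

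Early loss is not a remote possibility here. Acute medication is restricted from the start (Interventions), the Introduction says that withdrawal symptoms may lead to treatment failure, and the Objectives expect gastrodin to improve adherence. Early loss could thus differ by arm. If it does, and if those lost tend to do badly, a comparison of the remaining patients no longer reflects the randomised groups.

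The section also gives two answers for the same patient. Someone lost at week 2 is outside the efficacy set under its definition, yet is a treatment failure under the closing sentence. Whichever rule the analyst follows, the other is broken. For the remaining binary endpoints the text leaves open whether a lost patient is a failure or is imputed, and that choice can move the estimate.

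**Working it through.** **1. The two rules side by side.**

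| Patient | Set definition | Closing sentence |
|---|---|---|
| Dosed, lost before any evaluable visit | Excluded | Treatment failure |
| Dosed, one evaluable visit, then lost | Included | Treatment failure |
| Stops treatment but attends an evaluable visit | Included | Treatment failure if counted as not completing |

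Only the first row is in conflict.

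**2. The plan's own planning figure.** Inputs from Sample size: 46% against 22%, two-sided alpha 0.05, 90% power, Z-test with unpooled variance.

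n per arm = (1.960 + 1.282)² × (0.46×0.54 + 0.22×0.78) / 0.24² = 10.507 × 0.420 / 0.0576 = 76.6, so 77 as stated. Power at 77 is Φ(0.24/√(0.420/77) − 1.960) = 90.14% (stated: 90.188%). The 93 per arm follows as 77 × 1.2 = 92.4, rounded up. These proportions are used below only as a scale for a binary endpoint.

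**3. Early loss that differs by arm.** Assumptions: a share e of each arm is lost before any evaluable visit, and 62% of the rest are cured in both arms. The 62% is the control value for cured MOH in Table 2; the loss shares are not in the documents.

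- Planned set: 62% − 62% = 0.
- All randomised, losses coded as failures: 0.62 × (1 − e) in each arm, so gastrodin minus placebo = 0.62 × (e placebo − e gastrodin).

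| Early loss, gastrodin / placebo | All randomised, failure coding | Difference, points |
|---|---|---|
| 10% / 3% | 55.8% / 60.1% | −4.3 |
| 5% / 3% | 58.9% / 60.1% | −1.2 |
| 5% / 5% | 58.9% / 58.9% | 0 |
| 3% / 10% | 60.1% / 55.8% | +4.3 |

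The first row means about 9 against 3 patients of 93 (9.3 and 2.8). For scale, the standard error of a difference at 62% with 93 per arm is √(2 × 0.62 × 0.38 / 93) = 7.1 points, so 4.3 points is about 0.6 of a standard error.

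**4. Choice of rule when total loss is 20%.** Inputs: 46% against 22%, 93 per arm, and the 20% dropout allowance from Sample size. Its split by time and arm is assumed, and those rates are taken to hold among patients who are not lost.

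| Handling, 20% lost in each arm | Rates | Difference, points | Power |
|---|---|---|---|
| All lost patients excluded (about 74 per arm) | 46% / 22% | 24.0 | about 89% |
| Half lost early and excluded, half later and coded failure (about 84 per arm) | 40.9% / 19.6% | 21.3 | about 87% |
| All 93 kept, all losses coded failure | 36.8% / 17.6% | 19.2 | about 85% |

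In the middle row the rates are 0.46 × 0.8/0.9 and 0.22 × 0.8/0.9. With loss of 20% on gastrodin and 10% on placebo, failure coding gives 0.46×0.8 − 0.22×0.9 = 17.0 points; with the losses reversed it gives 0.46×0.9 − 0.22×0.8 = 23.8. Exclusion gives 24.0 in both cases, as does imputation under missing at random if loss is unrelated to outcome.

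**5. Primary endpoint.** A failure code has no value on a scale of headache days, so imputation is the only stated rule that can apply. A patient with no post-baseline data, imputed within arm under missing at random, adds information only through baseline. The estimate stays close to the one that leaves that patient out.

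**The case against.** The strongest defence is that the restrictions are stated openly, so no reader of the section is misled about who is analysed. The one-dose condition carries little risk under double blinding with matching placebo. A patient who stops treatment but attends one evaluable visit stays in the set. Drop-outs due to adverse events are counted separately as the tolerability outcome, and the safety set holds everyone dosed. All of this stands. It narrows the problem to patients with no evaluable visit at all, but does not remove it: they are randomised, and the section handles them in two ways.

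Three stronger readings are tempting, and the document does not support them.

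- A reader might infer that failure coding and imputation contradict each other outright. They need not. Treatment failure is a named endpoint, so the code can apply there and imputation elsewhere. What remains is that the rule for the other binary endpoints is unassigned; an analysis plan that is not shown may assign it.
- A reader might object that the set demands eDiary baseline data while Participant timeline lets baseline come from a "headache diary or face to face interview in outpatient clinic". That condition is settled before randomisation, patients who cannot supply a diary in screening are ineligible (Exclusion criteria), and Data collection methods bases the baseline survey on the eDiary. It should remove few patients and is unlikely to act differently by arm.
- A reader might apply the conflict to the whole dropout allowance, 186 × 0.20 = 37 patients. That is only a ceiling. The conflict reaches those lost before any evaluable visit, and the document gives no number for them.

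It is also fair to say that 4.3 points comes from one assumed scenario on a secondary endpoint, and that it is a bias only if the lost patients are properly regarded as not cured.

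**Conclusion.** The point holds in a limited form. The efficacy set is modified intention-to-treat under an intention-to-treat label, and patients lost before their first evaluable visit are both excluded and counted as failures. The handling of losses on cured MOH, 50% response and HIT-6 response is not assigned.

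The consequence lies mainly with the binary endpoints. In the assumed scenarios for cured MOH, the planned set and all-randomised failure coding differ by 0 to 4.3 points, in favour of whichever arm loses more patients early. On the planning proportions with 20% total loss in each arm, the choice of rule moves the expected difference between 24.0 and 19.2 points and power between about 89% and 85%. These sizes rest on assumed loss patterns and on failure as the outcome for lost patients. The primary estimate would hardly move under imputation within arm alone. The matter should be fixed before unblinding, but it does not by itself invalidate the trial.

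**What to change.** In Statistical methods:

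1. Make all randomised patients, analysed as assigned, the primary efficacy set.
2. Assign one missing-data rule per endpoint type. For treatment failure, cured MOH, 50% response and HIT-6 response, code non-completers and those lost to follow-up as failures. For headache days and the other continuous endpoints, use multiple imputation.
3. Add one sensitivity analysis for the continuous endpoints that departs from missing at random, for example placebo-reference imputation. Without it, the wider set will barely test the primary result.
4. Keep the present set as a sensitivity analysis, labelled modified intention-to-treat.

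The cost is a change of wording and one or two extra analyses, with no new data collection. The estimate may come out slightly less favourable to gastrodin.
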